### Adverse events and serious adverse events

The safety profile of ulinastatin was an important endpoint of the current study, partially because of the relatively large dose we chose. According to the package inserts of ulinastatin for injection, adverse drug reactions are uncommon (0.1% to 1%), including neutropenia, eosinophilia, nausea, vomiting, diarrhea, increased alanine aminotransferase, increased aspartate aminotransferase, injection-site tenderness, flushing, pruritus, rashes, and anaphylaxis [41].

It is recognized that the patient with sepsis will experience a number of aberrations in laboratory values, signs, and symptoms due to the severity of the underlying disease and the impact of standard critical medicine therapies. These will not necessarily constitute an AE unless they are considered to be of related to study treatment or a concern in the investigator’s clinical judgement. In this study, reporting of AEs will be restricted to events that are considered to be related to study treatment (possibly, probably or definitely).

Serious adverse events are defined as any untoward medical occurrence that meets one of more of the following criteria:Results in deathIs life-threateningRequires inpatient hospitalization or prolongation of existing hospitalizationResults in persistent or significant disability/incapacityIs a congenital anomaly/birth defect

The treating physician will be responsible for determining the causal relationship of the SAE as either definitely, probably, possibly, possibly not, or definitely not study treatment-related, as well as unclassified.

All treatment-related AEs and SAEs should be recorded on eCRF. SAEs will be reported to the Institutional Ethics Committee within 24 h of study staff becoming aware of the events.

The participants are provided with commercial clinical research insurance by the manufacturer of the study product.

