## Abstract

**Background:**

Sepsis is a major challenge in critical care and is associated with high mortality. Current management of sepsis and septic shock remains mainly supportive. Both basic and clinical research has shown that ulinastatin can improve the prognosis of sepsis. The aim of this trial is to evaluate the efficacy and safety profiles of ulinastatin compared with placebo.

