**Fig. 1 Fig1:**
[figure not shown]
Trial schedule of the ADJUST study. Eligibility screening includes diagnosis, inclusion/exclusion criteria, urine pregnancy test for female, demographics, medical history and physical examination,as well as the presence of shock, ARDS, SIRS, Acute Circulatory Failure, time from diagnosis of sepsis, number of impaired organs. Vital signs include blood pressure, body temperature, heart rate, respiratory rate. Lab tests include complete blood count, serum alanine aminotransferase, aspartate aminotransferase and serum creatinine. Inflammatory biomarkers include hs-CRP, IL-6, TNF-α and IL-10, which are sent to central lab for test.*intervention means blinded ulinastatin 400000 IU 3 times a day or matching placebo and usual care.#The timeframes for D14, D28 and D90 allow deviations of 1, 3, 7 days, respectively.

The following data will be recorded: demographics, sepsis diagnosis, concurrent medical conditions and comorbidities, inclusion and exclusion criteria, severity of illness and organ dysfunction scores, vital signs and laboratory results, potential confounding co-interventions (life-sustaining therapies, and use of other immunomodulatory agents), and outcomes (vital status at ICU and hospital discharge, day 28 and day 90, ICU and hospital length of stay).

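### AE reporting is limited to events judged treatment-related, so the comparison of non-serious AEs with placebo counts attributed events, and the eCRF rule for SAEs is ambiguous

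*Protocol article*

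**What the plan says.** The abstract states the purpose: "The aim of this trial is to evaluate the efficacy and safety profiles of ulinastatin compared with placebo". The section on adverse events and serious adverse events adds: "The safety profile of ulinastatin was an important endpoint of the current study, partially because of the relatively large dose we chose". The same section then sets these rules:

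- **What counts as an AE.** Aberrations expected in septic patients need not count as AEs unless they are thought to be caused by the study treatment or the investigator finds them clinically worrying. There are two routes in: relatedness, or clinical concern.
- **What is reported.** "In this study, reporting of AEs will be restricted to events that are considered to be related to study treatment". The qualifying grades run from possibly to definitely related. Only the first route remains.
- **SAEs.** They are defined by seriousness alone. The treating physician grades causality on a scale that reaches down to definitely not related and also has an unclassified category. SAEs go to the ethics committee within 24 h, with no condition on relatedness.
- **What goes on the eCRF.** "All treatment-related AEs and SAEs should be recorded on eCRF".

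The caption of Fig. 1 lists measurements taken irrespective of attribution: "Lab tests include complete blood count, serum alanine aminotransferase, aspartate aminotransferase and serum creatinine".

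**The concern.** In a blinded placebo-controlled trial the control arm supplies the background rate. A drug effect that resembles the disease shows up as an excess between arms, and nobody has to decide the cause in a single patient. Filtering on judged cause before recording gives up part of that advantage.

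It matters here because the protocol itself says that septic patients will have many abnormal values, signs and symptoms from the disease and its treatment. Several of the labelled reactions it lists are of that kind. A blinded assessor who sees diarrhoea or a transaminase rise in such a patient may reasonably put it down to sepsis, and it then does not reach the AE data.

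This is a stated recording rule, not a detail left open. A later analysis plan cannot recover non-serious events that were never recorded. At stake is the weight that a conclusion of good tolerability could bear, at a dose the protocol itself calls relatively large.

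**Working it through.** The plan gives no figure on this point, so there is none to reproduce. The check is a comparison of texts, followed by an illustration.

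**Step 1: definition against reporting rule.** An aberration that is a clinical concern but judged unrelated can be an AE under the definition. Under the next sentence it is not reportable. The two sentences do not agree on which events enter the data.

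**Step 2: what escapes the filter.**

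| Data | Subject to the relatedness filter? |
|---|---|
| Deaths (28-day, 90-day, ICU, hospital) | No |
| SOFA, six domains, baseline to day 28 | No |
| Vasopressors, ventilation, renal replacement | No |
| Blood count, ALT, AST, creatinine | No, scheduled tests |
| SAEs | Unclear for the eCRF; no filter for ethics committee reports |
| Non-serious AEs | Yes |

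SOFA has no gastrointestinal, skin, allergic or neutrophil domain. Of the labelled reactions, neutrophils, ALT and AST can be recovered from the scheduled tests. For nausea, vomiting, diarrhoea, flushing, pruritus and rash the article shows no route other than AE reporting.

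**Step 3: the eCRF sentence.** It can mean related AEs plus all SAEs, or related AEs plus related SAEs. A causality scale with unrelated categories, and a 24 h report without a relatedness condition, favour the first reading. The sentence itself does not settle it.

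**Step 4: illustration of lost sensitivity.** Inputs: 348 participants (sample size section), so n = 348/2 = 174 per arm if all are analysed; two-sided 5% test. The event rates and attribution shares are assumptions, not from the document. With p̄ = (p0 + p1)/2:

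- SE0 = √[2p̄(1 − p̄)/n]
- SE1 = √{[p0(1 − p0) + p1(1 − p1)]/n}
- power ≈ Φ[(p1 − p0 − 1.96 × SE0)/SE1]

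True rates are 10% (placebo) and 20% (ulinastatin). A share s of events is attributed equally in both arms, so the compared rates are 10% × s and 20% × s.

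| s | Rates compared | (p1 − p0 − 1.96 × SE0)/SE1 | Power |
|---|---|---|---|
| 1 | 10% vs 20% | (0.100 − 1.96 × 0.03828)/0.03790 = 0.659 | 74.5% |
| 0.5 | 5% vs 10% | (0.050 − 1.96 × 0.02824)/0.02811 = −0.190 | 42.5% |
| 0.25 | 2.5% vs 5% | (0.025 − 1.96 × 0.02037)/0.02032 = −0.734 | 23.1% |
| 0.1 | 1% vs 2% | (0.010 − 1.96 × 0.01303)/0.01302 = −1.194 | 11.6% |

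The risk ratio stays at 2 throughout. The absolute difference shrinks from 10 points to 5, 2.5 and 1.

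**Step 5: the same case with selective attribution.** Suppose 5% of background events and 50% of drug-caused events are attributed (also assumptions).

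- Placebo: 10% × 0.05 = 0.5%. Ulinastatin: 0.5% + 10% × 0.50 = 5.5%.
- (0.050 − 1.96 × 0.01829)/0.01809 = 0.782, power about 78%.

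With 10% and 50% the rates are 1% and 6%: (0.050 − 1.96 × 0.01970)/0.01952 = 0.583, power about 72%. Expected counts are small here (174 × 0.005 = 0.87 events on placebo), so the normal approximation is rough. The direction is clear: selective attribution can remove the loss.

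**Step 6: at the labelled frequency.** The article gives labelled reactions as 0.1% to 1%. For a 1-point excess, 10% vs 11% with every event counted, SE0 = 0.03287 and SE1 = 0.03286. Both tails give Φ[(0.01 − 0.06443)/0.03286] + Φ[(−0.01 − 0.06443)/0.03286] = 0.049 + 0.012, about 6%.

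**The case against.** Limiting AE reports in critical care can be a deliberate choice, and the article gives its reason: the disease and its treatment produce many aberrations. Judged possibly related is a low threshold for inclusion. At the labelled frequency the trial could hardly detect an excess even with complete recording (Step 6), and if attribution is reasonably selective little is lost (Step 5). All of this stands. It limits the size of the point and rules out asking for every ICU abnormality to be reported as an AE.

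A reader might infer more than the document supports:

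- *That organ toxicity would be filtered out before the arms are compared.* It would not, in general. SOFA, organ support, mortality and laboratory values bypass the filter, and the data analysis section compares SOFA and life-sustaining interventions between groups.
- *That unrelated SAEs go unrecorded, against the SAE definition.* This is one reading of one sentence, and most of the section points the other way. It is an ambiguity, not a demonstrated contradiction.
- *That the filter favours ulinastatin.* Subjects, investigators, nurses and coordinators are blinded, so under-capture is expected in both arms. Differential attribution would need drug effects that hint at allocation.
- *That the treating physician screens all AEs.* That role is stated for SAEs only; no assessor is named for non-serious AEs.

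How laboratory abnormalities are tabulated is commonly left to the analysis plan, which is not shown, so its absence from the article is no fault. What remains is the stated recording rule and its mismatch with the AE definition and the safety aim.

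**Conclusion.** The point holds in limited form. For non-serious AEs, the comparison with placebo will count events judged related. It may therefore under-capture drug effects that resemble sepsis, and what is not recorded cannot be restored at analysis. The expected harm is lost sensitivity. For SAEs, one sentence needs clarifying.

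The size is not established. The fall from 74.5% to between 42.5% and 11.6% rests on an assumed doubling from 10% to 20%, on 174 analysed per arm, and on attribution that thins background and drug-caused events equally. Other assumptions about attribution leave power about where it was. These figures show what could happen and are not estimates for this trial. The proposed change is worth making because it is cheap, not because a large loss has been shown.

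**What to change.** 1. Reword the eCRF sentence so that all SAEs are recorded and tabulated by arm regardless of causality.
2. Compare pre-set abnormality grades of neutrophils, ALT, AST and creatinine by arm, using the tests already scheduled and no attribution filter. If the analysis plan already does this, a cross-reference is enough.
3. Keep judged relatedness as a separate field and a secondary table.
4. Align the reporting sentence with the AE definition before it, so that sites know whether an event of clinical concern judged unrelated is to be reported.

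The cost is some extra SAE entry at sites and one more safety table, largely from data already collected. Non-serious symptoms such as vomiting or rash would still depend on attribution unless the sponsor also lists them for recording in both arms. If that is not done, the trial report should say that non-serious AE counts are counts of events judged related.

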### Data management

Data management will be performed by trained staff at each participating center using the electronic data capture (EDC) system (https://edc702.drugchina.org). The quality of trial data management will be guaranteed by the reliability, access control, and traceability of the EDC system. Data collection will be restricted to those variables necessary to define baseline patient characteristics (demographics, sepsis diagnosis, concurrent medical conditions and comorbidities, inclusion and exclusion criteria, severity of illness and organ dysfunction scores, vital signs, and laboratory results), the delivery of the study drugs, potential confounding co-interventions (life-sustaining therapies, and use of other immunomodulatory agents), and outcomes (vital status at ICU and hospital discharge, day 28, and day 90, length of stay in ICU and hospital). Randomized participants will be followed up until either death or 90 days after randomization, whichever comes first. Follow-up will be attended by study staff by either direct contact with the patient or their next of kin. Participants who withdraw from the study for any reason will be followed up according to the study follow-up schedule and analyzed on the ITT principle.

### Data monitoring and auditing

An independent contract research organization (H&J CRO International, Inc.) will be responsible for data monitoring. The quality assurance division of the same contract research organization will audit the trial regularly. This trial will be also audited by each Research Ethics Committee and China Food and Drug Administration.

### Statistical analysis

#### Sample size estimation

We reported the hospital mortality rate of 33.5% in a 2-month prospective cohort study of 484 patients with severe sepsis/septic shock in China [23]. We estimate that 28-day all-cause mortality will be 33.5% in the control group. Treatment effect was difficult to predict. Several meta-analyses of RCTs had suggested that ulinastatin treatment was associated with an odds ratio (OR) of 0.57 (95% CI 0.34–0.95) in hospital mortality among patients with severe sepsis/septic shock, despite the fact that the treatment effect was statistically insignificant, and all included studies were of low quality and published in the Chinese language [20, 22, 35, 42–45]. Moreover, Karnad and colleagues reported that 28-day all-cause mortality was 7.3% with ulinastatin vs 20.3% with placebo, corresponding to a RRR of 0.64. Based on these results, we presume that a treatment effect with a RRR of 0.40 to 0.45 might be plausible estimates. We calculate that an enrollment of 348 participants will have a power of 80% to detect an absolute reduction of 14.5% (relative risk reduction of 42%) in the study group compared to 33.5% of the placebo group, allowing for a loss to follow-up or withdrawal of 20%. Considering the prevalence of severe sepsis/septic shock in our patients, and assuming the rate of patient recruitment of one to two cases per month per center (with 12 participating centers), this trial will be finished within 2 to 3 years.

### Data analysis

All analyses will be performed according to the ITT principle. A *P* value < 0.05 is considered statistically significant. All tests are two-sided with no adjustment for multiple comparisons. Continuous variables are reported as means and standard deviations or medians and interquartile ranges. Categorical variables are reported as proportions. Pearson’s chi-squared test and adjusted multivariable analysis will be applied for the primary outcome. We plan to perform subgroup analyses for the primary outcome for predefined variables: presence or absence of septic shock, time from onset of sepsis to study enrollment (≤ 24 h or 24 to 48 h), and concomitant use of corticosteroids (yes or no). All the other data including age, APACHE II score, acute respiratory distress syndrome (ARDS) [46], systemic inflammatory response syndrome [47], acute circulatory failure [48], and number of failed organs will be presented as descriptive results. Pearson’s chi-squared test will be used for comparison of mortality outcomes between groups. The *t* test will be used for comparison of SOFA scores, life-sustaining interventions, lactic acid levels, fluid balance, inflammatory biomarkers, and function indicators between groups. A paired *t* test will be used for comparison of baseline and changes during the intervention.

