**Methods/design:**

In this multi-center, double-blind, randomized placebo-controlled trial we are recruiting a total of 348 subjects meeting “The Third International Consensus Definitions for Sepsis and Septic Shock” (Sepsis-3). Subjects will be randomized (1:1) to receive ulinastatin 400,000 IU three times a day for 10 days or matching placebo and usual care simultaneously. The primary outcome is 28-day all-cause mortality. Adverse events and serious adverse events will be monitored closely.

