### Randomization

Following informed consent and confirmation of inclusion and exclusion criteria, participants will be randomly assigned in a 1:1 ratio to receiving either ulinastatin or placebo, with the random assignments stratified according to institution and presence of septic shock. The definition of septic shock is sepsis and hypotension requiring vasopressor support to maintain a mean blood pressure of 65 mmHg or greater as well as having a serum lactate level greater than 2 mmol/L after adequate fluid resuscitation. Dynamic randomization will be carried out using a Distribution Annotation Interactive Web Response System through a central, secured website: https://iwrs104.drugchina.org. Minimization as the most common covariate-adaptive randomization was adopted in our trial, which derived from the method of Pocock and Simon [32]. The first subject will be assigned according to the simple randomization, then the allocation that produces the least total imbalance is chosen with a higher probability (*p* = 0.8) for each subject after the first one. Among the previous study the probability of *p* = 0.8 has been shown to be the most efficient [33]. The reason that we used minimization in the design is that the balance of 12 centers cannot be guaranteed by the conventional randomization, and different hospitals will be considered as a covariate in the statistical analysis. The allocation is blinded to both subjects and investigators, as well as nurses and clinical research coordinators. During the treatment period, the investigator will log on to the above website every day and be given a study drug box number. With this number, the investigator could pick out the study drug box for the specific day from local storage.

The investigator will unblind allocation to the ulinastatin or placebo group should treatment of study-related adverse events (AEs) require it. The unblinding process will be well documented and reported to the principle investigator, the clinical research coordinator, and the administrative staff, when necessary. Unblinded subjects will be included in the primary, ITT analysis.

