### Interventions

The study group and the control group will receive ulinastatin (400,000 IU every 8 h) and placebo, respectively, for 10 days, with the first dose administered within 8 h of study enrollment. In particular, the study drug is reconstituted with 10 ml of normal saline, which will be further diluted in 100 ml of normal saline. The study drug is administered over 1 to 2 h with the use of specially designed administration sets to ensure blinding. Matching placebo vials, with identical reconstitution and infusion instructions to the ulinastatin vials, will be administered on the same schedule. Apart from ulinastatin treatment, all enrolled patients will receive standard care for sepsis and septic shock as per local protocols, including, but not limited to, antimicrobial agents, intravenously administered fluids, enterally or parenterally administered nutrition, transfusion of blood and blood products, and life-sustaining therapy (e.g., vasopressors, mechanical ventilation, and renal replacement therapy). The treating physicians are encouraged to adhere to the updated Surviving Sepsis Campaign guidelines [34], although the final decision is at the discretion of the treating physicians.

Doses of ulinastatin showed significant variation in different clinical trials, from 300,000 IU [35] to 1,200,000 IU [36] daily. In a surveillance study of 17 ICUs of China Critical Care Clinical Trials Group (CCCCTG), 15 reported the use of ulinastatin as adjunctive treatment of sepsis, with daily dose range 200,000 IU to 2,000,000 IU ([name], personal communication). The safety and tolerance of multi-dose (up to 1,200,000 IU qid) of ulinastatin have been evaluated in healthy volunteers without any serious adverse events (SAEs) [37]. In a rat model of sepsis, treatment with high-dose ulinastatin (200,000 IU/kg) significantly inhibited the production of TNF-α, P-selectin, and thrombin-antithrombin complex compared with a low dose (50,000 IU/kg) [38]. In a previous clinical study, a high dose of ulinastatin (300,000 IU twice a day) was associated with a significantly better clinical outcome and cytokine assays compared with middle- and low-dose ulinastatin (200,000 and 100,000 IU twice daily, respectively) [39]. The dose of ulinastatin in this trial was determined by consensus based on the above evidence.

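### The blanket intention-to-treat rule has no exception for safety, so adverse events would be tabulated by assigned arm in all randomised patients; the effect is small and the fix is one sentence

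*Protocol article*

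**What the plan says.** The Data analysis section of the protocol article opens with a rule that carries no qualifier: "All analyses will be performed according to the ITT principle". The article names no other analysis population.

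Safety is within the scope of that rule. The abstract gives efficacy and safety as the aim and promises that "Adverse events and serious adverse events will be monitored closely". The section on adverse events says "The safety profile of ulinastatin was an important endpoint of the current study", partly because the chosen dose is relatively large. The same section narrows what is collected: "In this study, reporting of AEs will be restricted to events that are considered to be related to study treatment". Its SAE definition includes death, whatever the cause.

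Two design features bear on who is exposed to what:

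- Dosing starts after enrolment, "with the first dose administered within 8 h of study enrollment" (Interventions).
- Drug is dispensed daily: "the investigator will log on to the above website every day and be given a study drug box number" (Randomization). The investigator then takes that box from local stock.

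ITT is also mentioned in two narrower places: for unblinded patients, "Unblinded subjects will be included in the primary, ITT analysis" (Randomization), and for patients who withdraw (Data management).

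**The concern.** For efficacy, analysis by assigned arm protects the randomised comparison. For harm it is usually the less cautious choice, because it mixes patients without the exposure into the exposed group. Here it could act in three ways:

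- A patient randomised but never dosed cannot properly have a treatment-related AE, and so adds only to the denominator.
- A patient who dies between enrolment and the first dose can appear as an SAE in an arm whose drug was never given.
- A patient given the other arm's box has any resulting reaction counted under the wrong drug.

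The first and third shrink an AE risk difference. There is also a planning issue. Because the protocol fixes the rule for every analysis, an analysis plan that defined a treated-patient safety set would contradict it.

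**Working it through.** **Inputs from the protocol.** 348 patients randomised 1:1, so 348 / 2 = 174 per arm. Adverse drug reactions are put at 0.1% to 1% (package insert, cited under adverse events). AEs are recorded only if judged treatment-related. The protocol states no expected AE difference, so it has no figure on this point to reproduce; 348 is used only to get the arm size.

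**Inputs assumed.** The protocol gives neither u, the share of each arm never dosed, nor w, the share given the other arm's drug. I take u from 0 to 20% and w from 0 to 2%, equal in both arms. Treating w as full crossover is an upper-end choice, since one wrong box is one day of a ten-day course.

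**Model.** Let pt and pc be the treatment-related AE risks on ulinastatin and placebo, with zero risk if undosed. By assigned arm:

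- ulinastatin arm: (1 − u − w)·pt + w·pc
- placebo arm: (1 − u − w)·pc + w·pt
- difference: (1 − u − 2w)·(pt − pc)

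| u | w | Factor on the risk difference |
|---|---|---|
| 1% | 0 | 0.99 |
| 2% | 0 | 0.98 |
| 5% | 0 | 0.95 |
| 10% | 0 | 0.90 |
| 20% | 0 | 0.80 |
| 2% | 1% | 0.96 |
| 5% | 2% | 0.91 |

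**Example, with assumed risks of 15% and 5%** (difference 10 points, ratio 3.0):

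- u = 5%, w = 0: 0.95 × 15% = 14.25% against 0.95 × 5% = 4.75%. The difference is 9.5 points and the ratio is still 3.0.
- u = 5%, w = 2%: 0.93 × 15% + 0.02 × 5% = 14.05% against 0.93 × 5% + 0.02 × 15% = 4.95%. The difference is 9.1 points and the ratio 2.84.

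Only wrong-arm dosing moves the AE risk ratio. SAEs differ slightly: if undosed patients have SAE risk s, both arms gain the same u·s. That cancels from the difference but pulls the ratio toward 1.

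**Power in the same example** (two-sided 5%; 174 per arm by ITT, 174 × (1 − u) per arm as treated): 85.9% by ITT against 86.1% as treated at u = 5%, and 82.8% against 86.1% at u = 5%, w = 2%.

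**Rare reactions.** Expected cases of one reaction in 174 patients run from 174 × 0.001 = 0.17 to 174 × 0.01 = 1.74. With 2% wrong-arm dosing and a 1% reaction, the expected number of misplaced cases is 174 × 0.02 × 0.01 = 0.035. If one case did move, 2 against 0 would become 1 against 1. Even 2/174 against 0/174 has a Fisher p of 2 × (174 × 173) / (348 × 347) = 0.50.

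**The case against.** The strongest reply is that the protocol never describes an AE comparison. The tests in Data analysis cover mortality, SOFA, life support, lactate, fluid balance, biomarkers and function; AEs and SAEs are not listed. The other two mentions of ITT concern the primary analysis and withdrawals. A safety population is commonly left to the statistical analysis plan, which is not shown. This largely stands: the absence of a safety set is no finding, and a reader should not infer that a between-arm AE test by assigned arm is planned. What remains is that the rule covers every analysis, and tables for a declared important endpoint are analyses.

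Second, because AE reporting is limited to related events, undosed patients contribute no AEs, and pre-dose events can matter only for SAEs. That also stands. The recording instruction for SAEs is itself ambiguous: the restriction to treatment-related events may or may not extend to them, and if it does, unrelated pre-dose deaths would drop out. Deaths are in any case the primary endpoint, for which ITT is right.

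Third, two figures invite a larger claim:

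- The Background reports 4 discontinued interventions per arm in the earlier Indian trial, 8/122 = 6.6%. These are discontinuations and are not described as patients never dosed. The 20% in the sample size section is loss or withdrawal, also a different quantity.
- Daily dispensing means up to 348 × 10 = 3,480 box picks. That is a ceiling assuming every patient completes treatment, and no error rate is given.

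**Conclusion.** The point holds as a minor one. As written, the ITT rule reaches AE and SAE tables, and its effect on an AE risk difference is toward no difference. The size is modest: 1% to 5% shrinkage for an assumed 1% to 5% undosed, and about 9% with 5% undosed and 2% wrong-arm dosing. In the 15% against 5% example, the power cost relative to an as-treated analysis is 0.2 points from undosed patients at u = 5%, and 3.3 points when 2% wrong-arm dosing is added. All of this rests on shares that the protocol does not give, assumed equal in the two arms, and on counting a wrong box as full crossover.

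A reader might infer that the rule could hide or reverse a safety signal. The document does not support that. One misplaced case turns 2 against 0 into a tie, the expected number of such cases is far below one, and the sparse counts carry almost no inference either way.

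**What to change.** Limit the sentence to efficacy: *All efficacy analyses follow the ITT principle.* Then add: *AEs and SAEs are summarised in patients who received at least one dose, grouped by drug actually received, counting events from the first dose; deaths and SAEs are also shown by ITT.*

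Drug received should come from the recorded delivery of study drug, which Data management lists among the data collected. The box number issued by the web system is not enough alone: it shows which box should have been taken and cannot reveal a wrong pick. The rule for classifying a patient who received both drugs should be stated before unblinding. Counting any ulinastatin as ulinastatin is one convention among several.

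The cost is one changed sentence, one added sentence and one extra table. Safety and efficacy denominators may then differ by a few patients, which a footnote can explain.

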### Primary endpoint

The primary endpoint of this study is 28-day all-cause mortality.

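### 28-day mortality has two unranked analyses at the same 0.05 level, and the chi-squared test ignores both minimisation factors

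*Protocol article*

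**What the plan says.** The Primary endpoint section fixes the outcome: "The primary endpoint of this study is 28-day all-cause mortality".

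The Data analysis section gives it two analyses: Pearson's "chi-squared test and adjusted multivariable analysis will be applied for the primary outcome". Neither is called primary, confirmatory, supportive or sensitivity. The significance rule is a P "value < 0.05 is considered statistically significant", and "All tests are two-sided with no adjustment for multiple comparisons". Later in the same section, "chi-squared test will be used for comparison of mortality outcomes between groups", with no adjusted model mentioned.

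The Randomization section describes minimisation, "with the random assignments stratified according to institution and presence of septic shock". After the first patient, "the allocation that produces the least total imbalance is chosen with a higher probability" of 0.8. It adds that "different hospitals will be considered as a covariate in the statistical analysis". Septic shock, the other minimisation factor, appears in the Data analysis section only as a subgroup variable.

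**The concern.** Two issues arise.

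First, one endpoint has two P values and no rule for choosing between them. If one falls just below 0.05 and the other just above, the article does not say whether the trial is positive. The Background section criticises an earlier ulinastatin trial for a related weakness: its conclusion changed with the analysis population (P = 0.045 against 0.11). Here the open choice is the test.

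Second, minimisation makes the arms more alike on shock and centre than simple randomisation would. If those factors predict death, the chi-squared variance still includes variation that the allocation has largely removed. The test then tends to be conservative and loses some power. An analysis that includes the allocation factors recovers it.

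**Working it through.** **1. The plan's own figure.** Inputs from Sample size estimation: control 33.5%, treated 33.5 − 14.5 = 19.0%, 80% power, 20% loss, total 348. Two-sided 0.05 comes from Data analysis.

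- Pooled formula, mean rate 0.2625: n per arm = [1.96·√(2·0.2625·0.7375) + 0.842·√(0.335·0.665 + 0.19·0.81)]² / 0.145² = 144, so 288 in total. Multiplying by 1.2 gives 346; dividing by 0.8 gives 360.
- Unpooled formula: (1.96 + 0.842)²·(0.335·0.665 + 0.19·0.81) / 0.145² = 141 per arm, so 282 in total. Dividing by 0.8 gives 353.
- 348 less 20% is 278, or 139 per arm. Power there is 78.8%.

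The stated 348 is therefore in line with sizing on an unadjusted comparison of two proportions.

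**2. Simulation of the stated allocation.** From the article: 12 centres, shock as a second factor, probability 0.8, 1:1, control rate 33.5%. Assumptions not in the article: 50% of patients in shock, equal expected recruitment by centre, shock log-odds ratio 1.1 to 1.6 (odds ratio 3.0 to 5.0), between-centre SD 0.3 to 0.5 on the logit scale. Each data set was tested by chi-squared and by a logistic model with arm, shock and 11 centre indicators (Wald test). There were 4,000 null runs (Monte Carlo SE about 0.35 points) and 1,500 runs near the planned effect (SE about 1 point).

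Results with 278 patients, in %:

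| Shock log-OR / centre SD | Type I: chi-squared | Type I: adjusted | Type I: either | Power: chi-squared | Power: adjusted | Verdicts differ, null / effect |
|---|---|---|---|---|---|---|
| 0 / 0 | 5.3 | 5.7 | 5.8 | 79.5 | 80.1 | 0.7 / 1.7 |
| 1.1 / 0.3 | 4.5 | 5.5 | 5.5 | 82.1 | 84.8 | 1.1 / 3.4 |
| 1.1 / 0.5 | 4.5 | 5.7 | 5.9 | 82.3 | 85.3 | 1.5 / 3.7 |
| 1.6 / 0.5 | 3.6 | 5.4 | 5.4 | 80.4 | 84.1 | 1.9 / 4.4 |

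The mean risk difference under the effect was 14.5 to 14.9 points in the last three rows, slightly above plan. With 348 patients and the same three prognostic settings, chi-squared ran at 3.7 to 4.4%, the adjusted model at 5.3 to 5.5% and either test at 5.3 to 5.7%.

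A second set of runs (278 patients, shock odds ratio 3 to 4, centre SD 0.3 to 0.5) gave chi-squared 3.6 to 3.8%, adjusted 5.1 to 5.4%, either test 5.1 to 5.4%, and power of 80% against 82 to 83%.

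**3. Reading the power gain.** At 278 patients the gain is 84.8 − 82.1 = 2.7, 85.3 − 82.3 = 3.0 and 84.1 − 80.4 = 3.7 points. Part of it is test size. At a true size of 5.5% the critical value is about 1.92 rather than 1.96. At 80% power that is worth about 0.28 × 0.04 ≈ 0.011, or 1 point.

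**4. Reading the two-test inflation.** With only the minimisation factors in the model, either-test error exceeds the adjusted model's own error by less than 0.2 points in every row. The tests are so strongly correlated that the bound for two independent tests, 1 − 0.95² = 9.75%, does not apply. Adding a strong further covariate (1.0 logit per SD) raised either-test error to 7.7% at 278 patients and 7.2% at 348. The adjusted model alone was then already at 6.4% and 6.0%. Verdicts differed in 9.8% of trials at 278 patients under the effect.

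**The case against.** The best defence is that the article already points to chi-squared. It is listed first, repeated alone for mortality outcomes, and matches the sizing formula. On that reading the adjusted model is supportive, and model details belong in an SAP that is not shown. The covariate list and model form are indeed not at issue here. But these are hints, and the article never designates a decisive test. If chi-squared is the decisive test, it is one that ignores the factors used for allocation.

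Four stronger readings are tempting and are not supported:

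- *Data analysis contradicts Randomization over hospital.* The planned adjusted analysis can hold the hospital covariate, and nothing says that every test will be adjusted.
- *Two tests substantially inflate the false-positive rate.* With the minimisation factors alone the either-test rate is 5.1 to 5.9%. Higher figures need a strong extra covariate that the article does not name for the model.
- *Chi-squared threatens a false positive.* Its usual departure is towards caution, and not in every setting: in another set of runs one scenario gave 5.4%. The indicator-based logistic model itself runs slightly above 5%.
- *The trial forgoes power of about 87%.* That needs an APACHE II-type score at an assumed 0.8 logit per SD. It is not a minimisation factor, and Data analysis assigns APACHE II to descriptive reporting. Shock and centre alone account for about 2 to 4 points.

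**Conclusion.** The point holds at moderate size. The article gives the primary outcome two analyses at one significance level and names neither as decisive. One of them ignores both minimisation factors, and septic shock is nowhere named as a covariate. If shock and centre are prognostic as assumed, chi-squared has a type I error of about 3.5 to 4.5% and gives up about 2 to 4 points of power, roughly 1 of which may reflect the logistic model's size. The two tests would disagree in about 3 to 4% of trials of 278 patients at the planned effect. If neither factor is prognostic, there is almost no difference. The lack of a ranking rests on the text alone; the sizes rest on shock prevalence, shock effect and centre variation that the article does not give.

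**What to change.** Name one decisive primary analysis in the Data analysis section: logistic regression of 28-day death on arm, septic shock and centre, with one P value and a standardised risk difference with 95% CI. Pool small centres or fit centre as a random effect. At the planned rates 278 patients give about 278 × 0.2625 ≈ 73 deaths, or about 6 per centre, which is thin for 11 separate centre terms. Label chi-squared a sensitivity analysis, and bring its later mention for mortality outcomes into line. Use the same adjustment for 90-day, ICU and hospital mortality.

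Prespecified baseline age and APACHE II, already collected, could be added for a further gain, but the fix does not depend on them. Naming chi-squared as decisive would also remove the ambiguity, but would leave the mild conservatism in place.

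The cost is a slightly more complex model than a 2×2 table; no new data or larger sample is needed. The article reports recruitment as ongoing and plans no interim analysis, so the choice can be fixed before unblinding.
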